### Participants

Patients visiting the ED implementing the CM intervention are eligible if they are ≥18 years, able to communicate in a language that is spoken by the local team or a professional interpreter and have ≥5 ED visits in the past 12 months recorded. Exclusion criteria include presenting less than 2 vulnerability dimensions (i.e., social, somatic, mental, risk behaviors) besides frequent ED use, being unable to give informed consent, planning to stay in Switzerland less than 18 months, not expected to survive at least 18 months, awaiting for incarceration or being currently incarcerated, having a family member already enrolled in the study.

Given that this research study aims to disseminate and implement a CM intervention, we are neither aware of the number of hospitals that will eventually participate, nor of the number of participants who will be enrolled in each hospital.

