When first meeting the participant, the case managers will present the study and examine the exclusion criterion. If the patient does not have any exclusion criteria and is interested in participating, the case managers will conduct the informed consent process. After providing written consent, participants will receive the CM intervention. After each inclusion on site, the case managers will up-date the I-CaM research team in charge of the clinical assessment (i.e., baseline and follow-up assessments of the health-related variables to describe participants’ trajectories). The I-CaM research team will contact participants and conduct the baseline assessment within 10 days following the inclusion. Participants will then complete follow-up assessments at 3, 6 and 12 months post-baseline. All assessment interviews will be conducted by phone by bachelor-level students (i.e., of medical or social sciences) who will be trained and weekly supervised. For all patients, incentives (i.e., gift cards of 10, 20 and 20 CHF for the 3, 6 and 12-month follow-ups, respectively) and reminders will be used to compensate participation and obtain good retention rates. Other clinical variables (see measures section) will be directly extracted from medical records on-site by the I-CaM research team. Each site implementing the CM intervention will monitor their activities (e.g., tracking the number of eligible patients and the number who received the CM intervention). At the end of the operation phase, the research team will conduct semi–structured interviews with case managers and champions. Both champions and case managers will also complete a questionnaire.

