#### Clinical measures

As described above, the CM intervention aims at reducing ED visits and improving quality-of-life by targeting specific mechanisms, including empowerment, perceived self-efficacy, health literacy and motivation to change. Accordingly, participants will be assessed at baseline and at follow-ups on these clinical variables. Main outcomes will include ED use and quality of life, whereas empowerment, perceived self-efficacy, health literacy and motivation to change will serve as secondary outcomes. Please see Table 3 presenting a summary of clinical measures.

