##### ED visits

Number of ED visits over the past year will be extracted from medical records at baseline and at 12-months. Furthermore, ED visits over the past 6 months will be assessed at baseline, 6- and 12 months. ED visits at baseline will serve as covariate in the analyses, whereas the remaining measures will serve as outcome in the mains analyses.

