#### Clinical outcomes

Data will be screened for missing cases, outliers, and normality of distributions using descriptive statistics and plots. We will take appropriate steps to deal with missing data. First, we will conduct analyses to detect missingness patterns and test whether they may be considered “ignorable.” [48] If more than 5% of outcome data are missing, [49] we will divide the sample into 2 groups (i.e., missing, not missing), and use fully observed variables to predict missingness on the affected outcome. If fully observed variables are not significant predictors, missingness may be considered as “observed at random” and fulfilling some criteria for “missing completely at random” (MCAR) assumptions. In that case, we will use multiple imputations procedures for measured outcomes and direct maximum likelihood estimation for structural models. If data missingness is non ignorable (MNAR), we will use pattern-mixture models with multiple imputation to model the missingness mechanism.

Main analyses will comprise multilevel models (i.e., MLM; mixed effects model) [50] utilizing appropriate distributions for the outcome variables (e.g., Poisson, negative binomial, normal). MLM examine the effect of time (after receiving the CM intervention) on clinical outcomes (e.g., quality of life, self-efficacy). MLM is appropriate to handle nonindependence data. Specifically, data will be clustered by participants (i.e., repeated measures) and by hospitals. MLM does not assume independence of observations. Dependence is modeled through random effects (representing different sources of variability in the data). We will include sources of random variability at the group level accounting for between-group differences and another random effects for the individual accounting for within-person differences in the repeated measures. MLM will be adjusted for demographic variables (i.e., age and gender), ED use, at-risk behaviors (e.g., alcohol use disorders) and health status. Descriptive statistics will be conducted on SPSS and MLM on STATA. The significance level will be set at *p* = .05.

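### ED visits, a main outcome, are taken from on-site records with no named capture of visits to other EDs, so a change in where patients go can pass for a change in how often they go

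*Protocol article*

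**What the plan says.** The Clinical measures section sets the status of the outcome: "Main outcomes will include ED use and quality of life". The ED visits section gives the source and the windows. The yearly count reads: "Number of ED visits over the past year will be extracted from medical records at baseline and at 12-months". The half-yearly count reads: "ED visits over the past 6 months will be assessed at baseline, 6- and 12 months". Table 3 likewise gives medical records as the only tool for ED visits. The operation-phase section says where such records are read: "Other clinical variables (see measures section) will be directly extracted from medical records on-site by the I-CaM research team". No other ED, insurer or regional source is named, and no self-report of ED visits is listed.

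The Participants section requires that patients "have ≥5 ED visits in the past 12 months recorded", without saying in which ED or EDs. It excludes people "planning to stay in Switzerland less than 18 months, not expected to survive at least 18 months, awaiting for incarceration or being currently incarcerated".

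The analysis plan for clinical outcomes specifies mixed models "utilizing appropriate distributions for the outcome variables (e.g., Poisson, negative binomial, normal"), clustered by participant and hospital. It sets out steps for missing outcomes but does not mention death, departure or incarceration. The Limitations section discusses regression to the mean, self-report bias and retention. It does not discuss incomplete capture of ED visits.

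**The concern.** A count taken from one hospital's records measures visits to that hospital. It tracks total ED use over time only if the share of visits made there stays the same. In a randomized comparison a drift in that share would tend to affect both arms. Here the before-after difference is the effect estimate, so any drift goes straight into it.

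The article gives reasons not to take a constant share for granted:

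- The intervention sets out to redirect patients and change how they use services.
- Only hospitals that are interested take part, and the exploration phase plans interviews with hospitals that decline. Non-participating EDs in the same region are therefore foreseen.

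A visit moved to one of those EDs would be read as a visit avoided. Later analysis cannot repair this if off-site visits were never recorded.

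A smaller, related point is observation time. A record search for someone who has died, moved away or been incarcerated can return a low count that looks like a complete one. The article does not say how such windows are classed.

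**Working it through.** **Inputs.** The article gives no sample size, no off-site share and no exit rate, so there is no design figure to reproduce. The only related figure is the effect in the team's earlier randomized trial (section on case management effectiveness): 2.71 against 3.35 visits, and 2.71/3.35 = 0.809, which matches the stated 0.81. It serves only as a sense of scale, because it is a between-group ratio with a 95% CI of 0.63 to 1.02, not a pre-post change. All shares below are assumptions.

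**Step 1: off-site visits.** Let *a* be the share of visits made elsewhere before baseline and *b* the share after. The on-site ratio is then

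apparent ratio = true ratio × (1 − b)/(1 − a).

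With a true ratio of 1:

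| a (before) | b (after) | apparent ratio |
|---|---|---|
| 0 | 0.05 | 0.95 |
| 0 | 0.10 | 0.90 |
| 0 | 0.19 | 0.81 |
| 0.15 | 0.20 | 0.80/0.85 = 0.94 |
| 0.10 | 0.10 | 0.90/0.90 = 1.00 |
| 0.30 | 0.30 | 0.70/0.70 = 1.00 |
| 0.20 | 0.15 | 0.85/0.80 = 1.06 |

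The change in share drives the bias, not its level. The last row shows that the bias runs against the intervention if use becomes more concentrated at the study site.

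**Step 2: time at risk.** Suppose a share *f* of patients exits evenly over the 12 months and the empty record time is treated as observed.

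- 12-month count: on average half the year is lost per exit, so the ratio is 1 − f/2.
- Months 7-12: half of those who exit lose the whole window and half lose on average half of it, so 0.5 × 1 + 0.5 × 0.5 = 0.75 and the ratio is 1 − 0.75f.

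For f = 0.05 these give 0.975 and 0.9625; for f = 0.10, 0.95 and 0.925. To reach 0.81 by this route alone would need f = 2 × (1 − 0.809) = 0.38 on the 12-month count, or 0.191/0.75 = 0.25 on months 7-12. A 10% shift and 10% exits together give 0.90 × 0.95 = 0.855 over 12 months.

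**Step 3: can the planned interviews supply the missing visits?** Telephone interviews are scheduled at baseline, 3, 6 and 12 months. A 6-month recall item at baseline, 6 and 12 months covers the 6 months before baseline, months 1-6 and months 7-12. These match the half-yearly record windows. They do not match the yearly ones: the item would add 12 months of off-site visits after baseline but only 6 before. A total count is therefore comparable on the 6-month windows only.

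**The case against.** The strongest reply is that the documents show less than a reader might infer from them.

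- **That the five qualifying visits were at the study site, so the pre-count is concentrated there.** The entry rule names no site. The electronic alert in patients' files makes local counting plausible, but that is not stated.
- **That patients who die, leave or are incarcerated are scored as successes.** No rule sets their later visits to zero, and the analysis plan provides for multiple imputation and pattern-mixture models. The exclusions on survival, stay and incarceration also reduce foreseeable exits, though not unexpected death, moves within Switzerland or later incarceration.
- **That the absence of an offset is an error.** A person-time term is a detail that an article may leave to a fuller protocol or SAP not shown here. It can only be a point to confirm.
- **That the error always favours the intervention.** Step 1 shows it can run either way, and that a constant share does no harm.
- **That other EDs are excluded outright.** The text says on-site, not only on-site. One central team extracts at every site, so visits to other participating hospitals might be captured.

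Each of these stands and limits the claim. It is also fair that the Limitations section already commits to cautious interpretation of pre-post changes. That caution rests on regression to the mean, however, and does not tell a reader that off-site visits may be uncounted. None of the replies supplies a source for visits to non-participating EDs.

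**Conclusion.** The point holds as a gap in outcome capture. As written, a main outcome is drawn from on-site records in an uncontrolled pre-post design, with no named means of seeing visits to other EDs and no acknowledgement of this. A change in the off-site share after baseline biases the apparent change in ED use, and a shift towards other EDs would look like a reduction.

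The size depends on rates that the article does not give. Under no true effect and no off-site visits at baseline, shifts of 5% and 10% give ratios of 0.95 and 0.90. With some off-site use already present at baseline, the same 5-point change gives about 0.94 (15% to 20%), and an unchanged share gives 1.00. Lost observation time is the lesser issue: 10% exits would give 0.95 over 12 months, and only if empty record time is treated as observed, which the article does not say.

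**What to change.** 1. Add one item to the existing baseline, 6- and 12-month telephone interviews: the number of ED visits at other hospitals in the past 6 months, anchored to the same dates as the record windows.
2. Keep the on-site count as the main measure. Add a sensitivity analysis of total visits (on-site plus off-site) on the matching windows only: 6 months before baseline, months 1-6 and months 7-12. Do not build a 12-month total from this item.
3. Where possible, count visits at other participating sites from their records and leave self-report for the remainder.
4. Record dates of death, departure or incarceration where known, and confirm in the SAP that the count models use observed time at risk, for example through a log person-time offset.
5. Name incomplete capture of ED visits in the Limitations section.

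The cost is one question in calls already scheduled, a few dates, and one model term if it is not already planned. The downside is recall error in the self-reported part and non-response, notably from patients who die or are lost. Both counts should therefore be reported side by side, with the total read as a check on the on-site result and not as its replacement.

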#### The sustainability phase

Following the implementation of the CM intervention, the individual sites will continue the CM programs at their discretion. The research team will monitor the activity at each site and will be available for as-needed support to all sites. Clinical outcomes (i.e., ED use, quality of life etc.) will no more be measured. Finally, at the end of the sustainability phase, case managers and champions will participate in a final semi–structured interview with I-CaM team and complete a last questionnaire.

### Measures

#### Implementation-related measures

Table 2 summarizes the implementation measures by phase. Implementation-related measures will target both the implementation process evaluation (i.e., aiming to describe the process of the implementation and its influencing factors) and the implementation effectiveness evaluation (i.e., the extent to which the implementation was successful) and will include both quantitative and qualitative approaches.

**Table 2 Tab2:** Summary of the Implementation Measures by Phase

Components	Tool	Participants	Phase
Implementation process evaluation			
Implementation process	Stages of Implementation Completion (SIC)	Champions, case managers, I-CaM team	All
Implementation time-efforts and costs	Stages of Implementation Completion (SIC)	Champions, case managers, I-CaM team	All
Influencing factors			
ED staff awareness and interest in FUED and CM	Online survey	ED staff (public hospitals in the French-speaking Switzerland)	Exploration
	Semi-structured interview	Champions	Exploration
Acceptability, perceived appropriateness and feasibility of the CM	Acceptability Intervention Measure (AIM) and Intervention Appropriateness Measure (IAM) Feasibility of the Intervention measure (FIM)	Champions and case managers	Preparation and operation
	Semi-structured interview	Champions	Exploration
	Semi-structured interview	Champions and case managers	Operation
Intentions to use the CM	Measure of Innovation Specific Implementation Intentions	Champions and case managers	Preparation, operation
Implementation climate	Implementation Climate scale (ICS)s	Champions and case managers	Preparation, operation
	Semi-structured interview	Champions and case managers	Preparation, operation
Readiness for change	Organizational Readiness for Implementation Change (ORIC)	Champions and case managers	Preparation, operation
Implemention effectiveness			
Adoption rate (hospitals included/invited)	Monitoring of the activity on site	Hospitals	Exploration
Reach (patients receiving the CM/eligible)	Monitoring of the activity on site	Hospitals	Operation, sustainability
Implementation effectiveness			
Clinical effectiveness	Clinical outcomes (see Table 3)	Patients receiving the intervention	Operation
Fidelity of the CM	Fidelity checklist	Case managers	Operation and sustainability
Integration of the CM	NoMad survey	Champions and case managers	Operation, sustainability
	Semi-structured interview	Champions and case managers	Operation and sustainability
Normalization of the CM	Measure of Inner Context Sustainment (MICS)	Champions and case managers	Operation and sustainability
	Semi-structured interview	Champions and case managers	Operation and sustainability

##### Quantitative measures assessing implementation process

We will use an adapted Stages of Implementation Completion tool SIC [31] to assess implementation process by tracking the time of achievement of key implementation milestones over the whole implementation process. The SIC is a quasi-quantitative tool that measures progression of implementation activities (e.g., when engagement, provision of services and consultation begin) organized in eight stages, by recording the dates implementation activities were completed. The measure yields three main scores, a) the number of stages completed, b) the time spent in each stage and, c) the proportion of activities completed in each stage. Similarly, we will adapt and use the SIC to evaluate implementation time-efforts and costs by assessing the costs at each stages of the implementation process [32]. Specifically, the SIC will be used to track both hours put forth among staff involved in the implementation project on sites (e.g., case managers) and hours put forth from I-CaM; staff related to the implementation strategies. The measure yields full time equivalent and averaged salary costs scores. The SICs will be used over the whole implementation project.

Influencing factors will be evaluated among champions and case managers throughout the implementation process. As previously mentioned, in the exploration phase we will send an online survey to all ED services in the French-speaking Switzerland to evaluate ED staff’s interest and awareness related the FUED problem and CM intervention as well as their perceptions of needs regarding a CM intervention within their service. Additional influencing factors will be assessed at the end of the exploration, preparation and operation phases with the Acceptability Intervention Measure (AIM), the Intervention Appropriateness Measure (IAM), the Feasibility of the Intervention Measure (FIM) [33] and the Measure of Innovation Specific Implementation Intentions (MISII) scale (see Tables 2 and 3) [34]. Remaining quantitative measures at the preparation and operation phases include the Implementation Climate Scale (ICS) [35] and the Organizational Readiness for Implementation Change (ORIC) [36].

**Table 3 Tab3:** Summary of the Clinical Measures in the Operation Phase

Components	Tool	Timing
Descriptive variables and covariates		
Demographics	Self-reported questionnaire	Baseline
Vulnerability determinants	Extracted from medical records	Baseline
Clinical outcomes		
ED visits	Extracted from medical records	Baseline, 6, and 12 months
Health-care reorientation	Extracted from medical records	Baseline, 3, 6, and 12 months
Quality of life	WHOQOL-BREF	Baseline, 3, 6, and 12 months
Empowerment	Health Care Empowerment Inventory	Baseline, 3, 6, and 12 months
Self-efficacy	Self-Efficacy Scale	Baseline, 3, 6 and 12 months
Health literacy	European Health Literacy Project Questionnaire	Baseline, 3, 6 and 12 months
Problematic alcohol use	AUDIT-C	Baseline, 3, 6 and 12 months
Precursors of alcohol use	Visual analog rulers assessing importance, intentions, readiness and confidence regarding alcohol use changes	Baseline, 3, 6 and 12 months

##### Quantitative measures assessing the implementation effectiveness

The adoption rate at the conclusion of the exploration phase (i.e., the number of hospitals included in the research project) will be yielded by dividing the number of hospitals included in the research project by the number of hospitals invited to participate. At the operation and sustainability phases, reach will be yielded by dividing the number of patients receiving the CM intervention by the total number of eligible patients. Effectiveness will be examined using clinical outcomes assessed among patients receiving the CM intervention (see measures below). At the operation and sustainability phases, we will also examine the extent to which the intervention is provided as intended (i.e., fidelity to the CM intervention), using a checklist developed by the I-Cam research team of the core components of the CM intervention. This will be self-reported by the case-managers. Finally, we will examine integration and normalization of the CM intervention using the NoMad survey [37] and the measure of inner context sustainment (MICS) (in development and testing).

##### Qualitative measures

Implementation process will be further evaluated qualitatively during semi-structured interviews with champions and case managers examining influencing factors related the outer context (e.g., funding) and the inner context (e.g., organizational readiness to change, receptive context) [38, 39]. Finally, semi-structure interviews will also further examine the CM intervention normalization and integration [40], staff experience with the CM intervention training and coaching, and staff experience regarding the CM intervention implementation and delivery [41].

#### Clinical measures

As described above, the CM intervention aims at reducing ED visits and improving quality-of-life by targeting specific mechanisms, including empowerment, perceived self-efficacy, health literacy and motivation to change. Accordingly, participants will be assessed at baseline and at follow-ups on these clinical variables. Main outcomes will include ED use and quality of life, whereas empowerment, perceived self-efficacy, health literacy and motivation to change will serve as secondary outcomes. Please see Table 3 presenting a summary of clinical measures.

##### Demographic variables

Demographic variables (e.g., biological sex, age) will be assessed at baseline and will serve to describe the sample. They will also serve as covariates in the main analyses.

##### Vulnerability determinants

Vulnerability determinants refer to dimensions that have been found to be positively related to FUEDs [21]. Vulnerability determinants include social factors (e.g., lack of employment, limited social support), somatic factors (e.g., lower perceived health-related quality of life), mental factors (e.g., chronic mental disease), risk behaviors (e.g., alcohol and other drug use) and health-care use (e.g., frequent ED use). Vulnerability determinants will be assessed during the case management; they will therefore be extracted from medical records at baseline and will serve to describe the population and as covariates in the main analyses.

